#### Analyses of the secondary outcomes

Secondary outcomes will be computed according to the analysis strategy of the primary outcome using ANCOVA or logistic regression (depending on the scale of the respective outcome, continuous or dichotomous). Likely moderators will be added to the models including setting, and maternal attachment style and AAI reflective functioning. In order to investigate the longitudinal course until the 12-month follow-up, linear mixed models will also be calculated for the change of secondary outcomes (e.g., EPDS, PSI and PRFQ). In addition, sensitivity analyses are planned for the health economic analyses, in which the underlying unit-cost assumptions will be varied within realistic ranges.

#### Missing data

Analyses of primary and secondary endpoints will be conducted based on the FAS population without imputation of missing data. A sensitivity analysis is computed by imputing missing data of the primary outcome with multiple-imputation methods for linear regression using Markov chain Monte Carlo (MCMC) simulations. The selection of imputation variables will be decided blinded to treatment allocation and at least 5000 iteration and 100 imputations will be used.

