## Background

Parental mental health problems during infancy are known to impact children’s emotional well-being and to modulate future developmental trajectories [1–3]. Postpartum mental health problems show high prevalence rates. In the first year after the birth of a child up to 22% of all mothers develop a postpartum depression (PPD) [4], and nearly 21% of all women suffer from postpartum anxiety [1] or obsessive-compulsive illnesses [5] with a high comorbidity of these disorders [6]. Parental mental health problems have been identified as major factors for problems in parent-child interaction and as risk factors for the child’s well-being [7, 8]. In contrast, a positive mother-child relationship is an essential resilience factor for child development. Maternal sensitivity towards the infant is seen as a key variable in mother-child interaction and secure attachment development [9–11]. The lack of sensitivity and the low level of parental skills associated with PPD are known to affect the interaction with the child which has adverse effects on the child’s development [12]. According to Lyons-Ruth [2], these malignant patterns increase the risk of disorganized attachment patterns and produce child psychopathologies [13]. Recent reviews emphasize that this relationship might be more complex and dependent on the severity of the problems and the presence of additional risk factors [14]. The available evidence thus favors interventions that focus on altering maternal or paternal sensitivity which in turn are more effective in enhancing attachment security [1, 4, 14].

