### Trial design

The study will be designed as a two-arm, open, multi-center RCT with parallel groups and blinded endpoint assessment (PROBE design; prospective, randomized, open, blinded endpoint) with 6 weeks of intervention.

Depending on the severity of the psychopathological symptoms and in agreement with the participants’ preferences, the decision for a particular treatment setting (inpatient or outpatient) will be made before randomization. After assignment to treatment setting, participants will be randomly allocated to either the PIP intervention group or the CAU control group. A biometrician will independently carry out a 1:1 block randomization with variable block length and stratification by setting (inpatient or outpatient) and study center. Treatment allocation is masked to the assigning personnel and there will be no special criteria for discontinuing or modifying the allocated intervention. Data of mothers and children will be assessed at three measurement points (see Fig. 1): at baseline after randomization and immediately before the intervention (T0), after the intervention at 6 weeks (T1) and at 12-month follow-ups (T2). Study centers are located in the German cities Berlin and Flensburg. At the time of writing additional effort is being made for a study center in Hamburg.

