#### Secondary endpoints

*Child attachment*: the most important secondary outcome will be child attachment measured by the Strange Situation Procedure (SSP) [37]. SSP is a standardized procedure of eight episodes to record the quality of the child’s attachment. The aim of SSP is to activate the child’s attachment system. The test will be conducted in the laboratory, recorded on video, and will be coded by reliable and independent coders blind to treatment allocation. This will result in the classification of the quality of infants’ attachment behavior as being secure (B), avoidant (A) or ambivalent (C). In addition, coders are also trained to classify disorganized (D) attachment qualities. Because SSP can only be validly assessed starting at an age of 11 months, it will only be measured at the 12-month follow-up time-point. Group differences in child attachment will be examined using binarized SSP classification (secure/ insecure).

Because no cut-off values are available, dichotomous response variables for the EAS sensitivity scale at T1 and T2 will be computed using the Reliable Change Index (RCI) as additional secondary endpoints (RCI > 1.96, see [38]).

Further secondary outcomes for the maternal psychopathological symptoms:

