### Samples size calculations and statistical analyses

A power analysis [G*Power] based on a reported moderate to large effect size of Cohen’s *d* = 0.64 for a difference in maternal sensitivity after 6 weeks of intervention between the intervention group and the CAU group [19] and two-tailed testing with a significance level of *α* = 5% using an analysis of covariance (ANCOVA) (with maternal sensitivity at T1 as the dependent variable and maternal sensitivity at T0 as a covariate) resulted in a required sample size of *n* = 70 (per group) to detect an effect with a power of 95%. With an assumed drop-out rate of about 20% [1] the sample size calculates to *n* = 90 per group (total sample size *n* = 180 mother-child-dyads).

The statistical analysis will be carried out at the end of the last follow-up assessment and all analyses will be conducted in accordance *with intention-to-treat (ITT)* principles and will be including all randomized mother-child-dyads in the study. The *Full Analysis Set (FAS) will be used for all analyses (unless otherwise stated),* it will include all randomized mother-child-dyads. Data will be analyzed according to randomization irrespectively of the treatment received. Data from mother-child-dyads that have withdrawn from the study will be included in the FAS up to the date of their termination. The *Per-Protocol (PP) population* will comprise a subset of the FAS. It will consist of mother-child-dyads who will have received treatment according to the randomization, will have adequate therapy adherence, and no major protocol violations. Major protocol violations will be considered as not meeting all inclusion criteria, a change of treatment group or as the PIP intervention that has not been carried out properly according to the treatment manual. The *safety population* will include mother-child-dyads who have participated in at least one intervention session. Participants in the safety population will be analyzed according to the treatment actually received.

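### Attachment security at 12 months is analysed on observed cases only, while multiple imputation is confined to the 6-week outcome; extending it to attachment would use 6-week data that now enter no attachment analysis

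*Protocol article*

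**What the plan says.** The Secondary endpoints section ranks attachment first among the secondary outcomes: "the most important secondary outcome will be child attachment measured by the Strange Situation Procedure (SSP"). It is assessed only at the 12-month follow-up and analysed as secure versus insecure. The Secondary hypotheses section includes a higher rate of secure attachment under PIP.

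The Missing data section sets the general rule: "Analyses of primary and secondary endpoints will be conducted based on the FAS population without imputation of missing data". The one exception is a sensitivity analysis that imputes the primary outcome by methods for linear regression. The primary outcome is EAS sensitivity at T1, and the section on secondary analyses of the primary outcome gives imputation the same scope.

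Under Analyses of the secondary outcomes, binary outcomes get logistic regression following the primary strategy. For the longitudinal course, "linear mixed models will also be calculated for the change of secondary outcomes (e.g., EPDS, PSI and PRFQ"). No T1 variable is named for the SSP model.

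The Background gives the reason why T1 sensitivity should carry information about attachment: "Maternal sensitivity towards the infant is seen as a key variable in mother-child interaction and secure attachment development". The same article labels the secondary analyses exploratory.

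**The concern.** SSP security is the secondary endpoint most exposed to missing data. It is measured at the last visit, has no baseline value, and cannot enter a mixed model of change because it has a single time-point. It is also done in the laboratory, whereas the EAS play session is filmed at home, so SSP may be missing even for dyads still in follow-up.

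For dyads lost between T1 and T2 the trial will hold T1 sensitivity, EPDS, PSI and PRFQ. None of these enters a planned SSP analysis. If the dyads that leave one arm differ in T1 sensitivity from those that leave the other, the observed secure rates compare differently selected groups. At stake is the credibility of the result on a named hypothesis, although one with exploratory status.

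**Working it through.** **1. Numbers available at T2.** The protocol plans 90 dyads per arm, allocated 1:1, and assumes about 20% drop-out without saying at which visit. Its own step is 70/(1 − 0.20) = 87.5, so 88, stated as 90. At 20% loss, 90 × 0.80 = 72 dyads per arm would have an SSP; at 40% loss, 90 × 0.60 = 54. (The 70 per group is for the primary outcome. With d = 0.64, two-sided 5% and 95% power, recomputation gives 64 to 65, so 70 is conservative. This does not bear on the present point.)

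**2. Sampling error.** Assume 50% secure in each arm (not in the protocol).
- SE of the difference = √(2 × 0.25/n).
- n = 72: √0.00694 = 0.083, or 8.3 points; 95% interval about ±16 points.
- n = 54: √0.00926 = 0.096, or 9.6 points.

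**3. Bias when loss depends on T1 sensitivity in one arm only.** Large-sample simulation, 600,000 dyads per arm. From the protocol: a T1 effect of 0.64 SD. Assumed: latent correlation of T1 sensitivity with security 0.2 to 0.4, log-odds of loss changing by 1 per SD, loss of 20% to 40%, all of it after T1, and PIP acting on attachment only through sensitivity. The true difference is then about 5 to 10 points.

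| Correlation | Loss | Bias, low-sensitivity CAU dyads leave | Bias, low-sensitivity PIP dyads leave |
|---|---|---|---|
| 0.2 | 20% | −1.4 | +1.4 |
| 0.4 | 20% | −2.8 | +2.8 |
| 0.4 | 40% | −5.3 | +5.2 |

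Relative to sampling error: 1.4/8.3 = 0.17 and 2.8/8.3 = 0.34 standard errors at 20% loss, which lowers the coverage of a 95% interval to 94.7% and 93.7%. At 40% loss the worst case is 5.3/9.6 = 0.55 standard errors.

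**4. A second model.** Here security follows a logistic model with a slope of 0.5 to 1.0 per SD of T1 sensitivity, 50% secure under CAU and a T0–T1 correlation of 0.5. On a latent scale these slopes equal correlations of 0.5/√(0.25 + 3.29) = 0.27 and 1/√(1 + 3.29) = 0.48, so the upper end is a stronger link than in step 3.
- Loss tied to sensitivity in CAU only, 20%: 7.3 becomes 5.2 and 12.9 becomes 9.3 points (bias 2.1 and 3.6).
- Same mechanism in both arms, 20%: 7.4 becomes 6.6 and 12.9 becomes 11.6 (bias 0.8 and 1.3). At 30%: 7.4 becomes 6.3 and 12.8 becomes 10.7 (bias 1.1 and 2.1). With no PIP effect, the bias is nil.
- Opposite mechanisms in the two arms, 20%: 7.7 becomes 3.7 and 12.9 becomes 6.2 (bias 4.0 and 6.7). This is an extreme case.

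**5. Does using T1 help?** In every scenario of step 4, weighting the observed cases by the inverse of their true probability of staying, given T1, restored the full-data odds ratio to within about 0.02. This stands in for any method that uses T1 correctly, such as multiple imputation. It is a best case, because the simulated loss depends on T1 alone.

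**The case against.** Several points against the concern stand.

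- **Nothing shows that T1 data predict loss.** A reader might infer that they do, and so that the comparison is biased. The protocol's limitations section links withdrawal to engagement and therapeutic alliance, and adds that alliance and motivation will not be measured. Loss that runs through those would not be fully corrected by imputing from EAS and EPDS.
- **Some loss may occur before T1.** The only drop-out figure is attached to the sample size for the T1 outcome. Dyads lost by then have no T1 data. The protocol gives no T1–T2 rate, 40% is twice its only figure, and it plans retention measures (compensation up to the 12-month visit, contact by the study nurse).
- **The bias is small beside sampling error** at the 20% that the protocol assumes.
- **Expressing the bias as a share of the effect misleads.** The 5 to 10 points come wholly from 0.64 SD and an assumed correlation. The Background cites a review in which PIP improved attachment security without a difference in sensitivity, so another path to attachment is possible and the ratio would change.
- **It would be too strong to say that the plan discards T1 data or could show no sign of the problem.** Mixed models use the T1 scales, and withdrawals are to be documented and to contribute to the analyses. What holds is narrower: none of this feeds an SSP analysis.

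The exploratory label and the unseen analysis plan weaken the point but do not remove it. The article states a rule for secondary endpoints and names the single outcome to be imputed, so this is not a detail left open.

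**Conclusion.** The concern holds in a limited form. By stated rule, the most important secondary outcome is analysed on observed cases, and T1 data on dyads lost between T1 and T2 enter no SSP analysis. The secure/insecure comparison can be biased if loss after T1 depends on T1 sensitivity differently by arm. With dependence in one arm only, the size is about 1.4 to 2.8 points at 20% loss and up to about 5 points at 40%, in either direction. A somewhat stronger sensitivity–attachment link gives up to 3.6 points at 20%. The standard error at 20% loss is about 8 points. With one mechanism common to both arms the bias is about 0 to 2 points, and none under the null.

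The correlations, loss mechanisms and post-T1 loss rates are all assumptions. The protocol supports a possible bias, not an expected one. The change is worth making because it is cheap and uses data already collected, not because the planned analysis is shown to fail.

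**What to change.** Extend the planned multiple-imputation sensitivity analysis to SSP security at T2.

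- **Model.** Use a logistic imputation model, since the present text covers linear regression only. Include arm and a small set of predictors fixed before unblinding: T0 and T1 EAS sensitivity, T1 EPDS, setting, and T2 EAS where available. That is six terms; with 144 observed SSPs at 20% loss and about half secure, 72/6 = 12 outcomes in the smaller category per term. A wide model fitted separately by arm (four scales at two visits plus age, setting and centre, 11 terms) would have about 36/11 ≈ 3 and should be avoided.
- **T1 variables.** Use them only in the imputation model. They are measured after randomisation and may carry part of the treatment effect, so they should not be covariates in the attachment model.
- **Reporting.** Present the imputed result beside the observed-case logistic regression, and state before unblinding which one leads. Do not let the choice depend on whether they differ.

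The cost is a few lines of text and modest analysis time; no new data are needed. The drawback is one more model to specify. It assumes that the recorded data explain the loss, and it does little for dyads lost before T1.

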### Methods to minimize bias

Data will be stored electronically at SEGC and will remain blind for treatment allocation for all researchers and coders. The database of participant information and allocation will be maintained by the SKKIPPI study nurse at the study center in Berlin. The study nurse will be the only person who will have access to the participants’ personal data and the treatment allocation list. To minimize research bias only trained psychologists will notify mothers about the allocation outcome. Data will be collected by trained researchers who will be blind for randomization and treatment allocation and who will not be involved in the treatment of the mother-child-dyad.

The study sets a high standard in PIP treatment and minimizes therapeutic bias and attrition insofar that all study therapists will be trained in the manual before the beginning of treatment and will take part in monthly supervision by experienced PIP therapists. For monitoring the therapeutic process, all therapists will complete the Treatment Adherence Questionnaire after each treatment session. In order to create a good therapeutic alliance, therapists will provide a comfortable and trustful atmosphere. It will be ensured that the patient is aware of their therapeutic progress and own expectations. To minimize bias for the assessments, most of the data will be assessed electronically and stored in a secured database supervised by the SEGC. In addition, the study has a strict separation of research assessments and therapeutic intervention and researchers are well-trained in the assessment methods.

### Ethical considerations and limitations

Data will be assessed, processed and stored according to the data protection laws and the local data protection protocol. The research project will be carried out in compliance with the study protocol and the Declaration of Helsinki (1996 version, Somerset West). All researchers and participants in the study are obliged to follow the rules of Good Clinical Practice (ICH-GCP). Participants will only be enrolled in the study after giving inform consent. The study is designed as an open RCT with blinded endpoint assessment and blinded analysis. Still, participants will be aware of their treatment group allocation.

This trial compares a psychotherapeutic intervention with available CAU interventions. The CAU interventions will be heterogeneous and administered under very diverse conditions. Therefore, it will be difficult to document which component of CAU is most effective. Moreover, there will be differences in CAU depending on the setting (inpatient vs. outpatient). Due to ethical concerns participants will not be randomly allocated to a setting. Thus, more severe cases will be evident in the inpatient setting, lowering the representativeness of the results. At the same time the CAU routine intervention will be more intense in inpatient departments, i.e., CAU in inpatient settings will likely include other (psycho-)therapeutic interventions. Furthermore, ethical consideration precluded the inclusion of a waiting-list group. This very same concerns will also lead to the fact that all mother-child-dyads allocated to CAU will be offered an intervention or CAU. Thus, the standard in the CAU will likely be higher than in the overall population in Germany which will bias generalizability of the results. In order to minimize these effects and to incorporate these limitations in the analyses, all interventions in all conditions will be documented.

There is a lack of good quality trials for the proof of efficacy of PIP in the treatment of mothers [15] but more specifically of fathers [24]. This present study is designed for mothers with postpartum mental disorders. The importance of the fathers’ involvement for treatment outcomes, for the family system and the impact on child’s development is not assessed, neither will father-infant-dyads be included in the study. Following the study by Letourneau [50, 51] mothers with PPD report that fathers are a key resource for support. Until now, little is known about the fathers’ effects on the system, and with the present design no conclusions regarding fathers can be drawn.

A further limitation of this study is the eligibility of a diverse range of maternal postpartum diagnoses which will likely lower the power to detect effects. On the other hand, this design was chosen because of the higher generalizability when not restricting inclusion criteria to single diagnoses. If sufficient data are available, exploratory analyses of subsamples with the same diagnoses are intended. The PIP intervention in the present study has been designed as a short-term treatment of 12 sessions for parent-infant-dyads. Short, sensitivity-based interventions have been shown to have superior efficacy compared with longer ones [15, 19]. Still, in the case of a highly traumatized mother it might be less effective. Of note is also that study therapists and participants will not be blind to treatment allocation.

Some studies [23, 52–54] point out that there is a link between the engagement of participant, withdrawal and therapeutic alliance. In this trial, therapeutic alliance and patients’ motivation will not be assessed. But all withdrawals and severe events will be documented and contribute to the statistical analyses.

## Discussion

Interventions with a focus on attachment and maternal sensitivity and, in particular, parent-infant-psychotherapeutic interventions, have a good evidence base for the treatment of mental health problems in the postpartum period [15, 19] and the foundation of healthy child development. Given the high prevalence of postpartum mental disorders in mothers and the adverse impact on the child, a high-quality study focusing on the efficacy of PIP in Germany is needed. PIP in inpatient psychiatric departments has not been in the focus of controlled trials so far, and the present study differs to previous ones in that no particular risk samples are examined (like social adverse samples [1] or imprisoned mothers [25]) but diagnosed mothers with mental disorders in the postpartum period. There is a strong focus on prevention studies in early childhood in the German health care services. For the particular case of mental disorders, the trial is expected to reveal the efficacy of PIP in comparison with CAU in inpatient psychiatric settings and also in outpatient home visits to contribute to the ongoing discussion in the German health care system. As a further result, it will be expected to provide information for practitioners, and mothers and fathers on factors contributing to the efficacy of PIP interventions and to improve the future care situation for patients and their families in Germany.

### Trial status

The recruitment for the trial started in January 2019 and is ongoing (as of May 2020). It is expected to be completed in September 2021. This protocol is version 1.0, dated 13 September 2018.

## Data Availability

Trial results will be published in peer-reviewed journals regardless of outcome and will be presented at national and international conferences. An accessible summary of the findings will be published for participants, and members of the public at the project website skkippi.de. The data sets analyzed in the current study will be made available from the corresponding author on reasonable request in anonymized format only. A model consent form and other related documentation given to participants and authorized surrogates will be available from the corresponding author on reasonable request.

